# Low-carbohydrate diet in the treatment of type 2 diabetes mellitus (LoCaT): study protocol for a multicenter, randomized controlled trial

**DOI:** 10.1186/s13063-023-07427-5

**Published:** 2023-06-19

**Keywords:** Type 2 diabetes mellitus, Randomized controlled trial, Study protocol, Low-carbohydrate diet, Canagliflozin

## Abstract

**Background:**

Low-carbohydrate diet (LCD) is an emerging therapy for type 2 diabetes mellitus (T2DM). Although its effect on glucose control has been confirmed in previous clinical trials, most of those studies have focused on comparing calorie-restricted LCD to iso-caloric low-fat diets. In this study, we aim to compare the effects of LCD and canagliflozin, a sodium-glucose cotransporter 2 inhibitor, in patients with T2DM.

**Methods:**

This is a multicenter, randomized controlled trial. We will recruit 120 patients with poor-controlled T2DM. Participants will be randomly divided into canagliflozin and LCD groups in a 1:1 ratio. The primary outcome is the change in hemoglobin A1C levels after the 3-month intervention. The secondary outcomes are the time in range and cost of antihyperglycemic agents. Exploratory outcomes include physical examination, body composition, glucose variability, appetite, glycolipid metabolism, liver lipid content, and urine glucose threshold.

**Discussion:**

No previous study has compared an LCD with antihyperglycemic agents. In LoCaT, participants’ metabolism will be assessed from multiple perspectives. It is believed that the finding obtained from this trial will optimize the treatments for patients with T2DM.

**Trial registration:**

Chinese Clinical Trial Registry ChiCTR1900027592. Registered on November 20, 2019.

**Supplementary Information:**

The online version contains supplementary material available at 10.1186/s13063-023-07427-5.

## Background

Diabetes mellitus (DM) is one of the most common metabolic disorders worldwide, and its prevalence is increasing annually. In 2019, 463 million adults (20–79 years) were estimated to have diabetes [1]. The prevention and treatment of diabetes have become a growing public health challenge. The current management of diabetes includes lifestyle interventions, medications, and bariatric surgery. Lifestyle interventions mainly include diet modification and exercise, and the low-carbohydrate diet (LCD) is currently one of the most popular dietary interventions for diabetes.

LCD requires carbohydrate intake lower than 26% of total daily energy intake without limitations on protein and fat intake. The antihyperglycemic efficacy of LCD reported in different studies varies significantly. For example, a study involving 400 people found that 10-week LCD (carbohydrate intake < 30 g/day) reduced fasting blood glucose by 1.9 mmol/L and glycated hemoglobin A1C (HbA1c) by 1%, 87% of the patients reduced or stopped insulin therapy, and the dose of oral antihyperglycemic agents was also reduced to different degrees [2]. In addition, a meta-analysis showed that LCD (carbohydrate < 26% of total energy intake) decreased HbA1c by 0.47%, 0.36%, and 0.17% at 3 months, 6 months, and a year, respectively, while moderate carbohydrate diets (26–45% of total energy intake) reduced HbA1c by only 0.06%, 0.06%, and 0.08% at 3 months, 6 months, and a year, respectively [3]. Notably, we observed significantly better efficacy of LCD in improving blood glucose levels in clinical practice than previously reported. However, previous clinical trials have often focused on comparing LCD to low-fat diets rather than blank controls or positive controls. Therefore, we designed this trial to determine the effect of LCD in patients with type 2 diabetes mellitus (T2DM) by comparing it with a positive control drug.

In the past few years, sodium-glucose cotransporter 2 inhibitors have become a new class of antihyperglycemic agents. They reduce the reabsorption of glucose in the kidney, excrete excess glucose to urine, and lower plasma glucose levels. In addition, large clinical trials have also shown that sodium-glucose cotransporter 2 inhibitors can increase plasma ketones and reduce body weight [4]. Notably, both LCD and sodium-glucose cotransporter 2 inhibitors have ketogenic effects. Thus, in this trial, canagliflozin, a sodium-glucose cotransporter 2 inhibitor, will be used as a parallel control for LCD, and its effects on blood glucose levels and metabolism will be compared.

Metabolic syndrome is a cluster of abdominal obesity, insulin resistance, hypertension, and hyperlipidemia [5], and it is common in patients with T2DM. Therefore, this trial will also compare the efficacy of the two interventions in weight loss, insulin sensitivity improvement, blood pressure reduction, islet β-cell improvement, and dyslipidemia management.

The main purpose of this trial is to compare the antihyperglycemic efficacy of LCD and canagliflozin. In addition, blood glucose fluctuations will be evaluated by continuous glucose monitoring and pharmacoeconomics. Moreover, the trial will also explore the effects of the two interventions on body fat, blood pressure, liver and kidney function, appetite, and urine protein and their clinical safety profiles. This trial innovatively adopts canagliflozin as the positive control for LCD, and it will provide solid evidence for the application of LCD in patients with diabetes mellitus.

## Methods/design

### Design

LoCaT is a multicenter, randomized, positive-controlled, parallel-group, and non-inferiority trial. Participants will be recruited from three academic hospitals in China: Shanghai Sixth People’s Hospital Affiliated to Shanghai Jiao tong University School of Medicine, Shanghai Eighth People's Hospital, and Ningbo First Hospital.

A total of 120 participants will be enrolled in the study. Competitive enrollment was used to recruit participants, with an allocation ratio of 1:1 for the canagliflozin and LCD groups. The participants will receive the intervention, and data will be collected. The report will be written according to Standard Protocol Items: Recommendations for Interventional Trials [6].

### Objectives

The primary objective of LoCaT is to evaluate whether LCD has a similar effect as canagliflozin on glucose control based on the change of HbA1c from baseline to the end. The secondary objectives are glucose variability and expense change of antihyperglycemic agents after a 3-month intervention.

### Participants

#### Inclusion criteria

Voluntary participation and signed informed consent18–70 years of ageDiagnosis of T2DM according to the 2019 American Diabetes Association standards [7]Glycated hemoglobin ≥ 7.5% and ≤ 11%Willing to accept canagliflozin or LCDPlasma β-hydroxybutyric acid ≤ 0.3 mmol/L or negative urine ketone

#### Exclusion criteria

Diabetic ketoacidosis-related causes such as a history of myocardial infarction, chronic pancreatitis, stomach cramps, or alcohol abuse (drinking more than three standard cups per day or at least one time drinking more than five standard cups per week)History of other metabolic diseases (such as thyroid dysfunction and Cushing’s syndrome)Type 1 diabetes mellitusThe average proportion of carbohydrates in the diet < 40% in the past 6 monthsThose with fatty acid transport and oxidative disorders, such as carnitine deficiency and porphyriaHistory of symptomatic cholelithiasis (except for cholecystectomy)History of lower extremity infection, gangrene, and foot ulcersAlanine transaminase and/or aspartate aminotransferase > 3 times the upper limit of normal or patients with active liver diseasesEstimated glomerular filtration rate ≤ 60 mL/(min·1.73 m.^2^)Patients with urinary tract infectionsMalignant tumors occurring within 2 yearsPregnant or lactating womenThose who are participating in or have participated in other clinical studies within 4 weeks before the start of the studyThe researcher believes that the participant has a disease that affects the outcome assessment or is unsuitable for enrollment.

### Sample size

This is a non-inferiority trial, and the primary outcome is the change in HbA1c from baseline (△HbA1c) to 13 weeks after treatment. According to previous studies and our pilot study, the standard deviation of △HbA1c was estimated as 0.73 for both groups [8–10]. Sample size was calculated using PASS software (version 11.0), with an alpha of 0.025 and beta of 0.2, and 54 samples per group were needed. Considering a 10% loss during follow-up, a total of 120 samples is reasonable for this study.

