### Statistical analysis

This study will analyze both the full analysis (FAS) set and per-protocol set and accept the non-inferiority hypothesis only if it is confirmed in both samples. Multiple imputations will be used to handle missing data in the FAS. To avoid potential bias in the results, which may be due to methodological decisions or our datasets, we will perform a sensitivity analysis. Subgroup analyses will be performed according to HbA1c levels, medication history, and diabetes duration. Statistical analysis will be performed using SPSS Ver.21.0 software. Data are presented as mean ± standard error or median (25th–75th percentiles) for continuous variables and as percentages (%) for categorical variables. Baseline and endpoint differences between groups will be analyzed using the independent *t*-test or Mann–Whitney *U* test for continuous variables and the chi-square test for categorical variables. Comparisons within each group (before and after the 3-month intervention) will be performed using a paired *t*-test or Wilcoxon test. Statistical significance will be set at *P* < 0.05. This study will not include interim analyses.

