## Discussion

Antihyperglycemic drugs are currently commonly used for diabetes treatment. However, to date, no trials have compared LCD to antihyperglycemic drugs. Therefore, we will conduct this trial to determine the comparative effects of LCD. Among many antihyperglycemic drugs, sodium-glucose cotransporter 2 inhibitors show similar effects, such as ketogenesis and weight loss, as those of LCD. Among the sodium-glucose cotransporter 2 inhibitors, canagliflozin has the highest capacity for promoting glucose excretion. Therefore, this trial will compare LCD with canagliflozin to evaluate the efficacy of LCD in terms of glycemic control, insulin resistance, and lipid metabolism.

LoCaT is designed as a non-inferiority trial since LCD is more life-altering and patient compliance may not be good. If LCD does not achieve similar effects as canagliflozin, it can be replaced by antihyperglycemic drugs. Therefore, a prerequisite for the clinical application of LCD is that it should have an efficacy similar to that of canagliflozin. Therefore, a non-inferiority study is designed. If the trial results ultimately show that LCD has achieved non-inferiority and may even surpass canagliflozin, we will conduct a superiority analysis.

Although previous studies continuously monitored blood glucose levels after treatment with LCD or sodium-glucose cotransporter 2 inhibitors, only 48-h data were available [13, 14]. Glucose variability is considered an independent driver of increased oxidative stress and inflammation, a predictor of macrovascular and microvascular complications, and an independent risk factor for the prevalence and mortality of cardiovascular events in T2DM [15–17]. In LoCaT, participants will be required to continuously monitor glucose levels by the sensor at the initial and end states of intervention for 14 days so that glucose fluctuation before and after intervention can be observed. Glucose improvement, variability indices, and safety-related indices will be analyzed comprehensively.

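### The non-inferiority margin and the assumed true difference are not stated, so the primary verdict has no bound and 54 per arm cannot be checked

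*Protocol article*

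**What the plan says.** Under Sample size, the protocol article declares the hypothesis: "This is a non-inferiority trial, and the primary outcome is the change in HbA1c from baseline". The SD of that change "was estimated as 0.73 for both groups", and the calculation was run in PASS "with an alpha of 0.025 and beta of 0.2, and 54 samples per group were needed". A 10% allowance for loss to follow-up brings the total to 120.

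Under Statistical analysis, both the full analysis set (FAS) and the per-protocol set (PPS) are used, and the trial will "accept the non-inferiority hypothesis only if it is confirmed in both samples". The between-group methods listed there are the t-test, the Mann–Whitney test and the chi-square test, with a general significance level of P < 0.05. Missing data in the FAS are multiply imputed.

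Elsewhere the aim is put only in words. Objectives: "evaluate whether LCD has a similar effect as canagliflozin on glucose control". Discussion: "it should have an efficacy similar to that of canagliflozin". No section gives the largest deficit that would still count as non-inferior, or the true difference assumed in planning.

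**The concern.** The margin is the null hypothesis of a non-inferiority trial. Without it, the both-sets rule refers to a hypothesis that the document never defines, and the only numerical criterion left is P < 0.05 for a difference. A non-significant difference does not show non-inferiority, yet a reader who has only the words about a similar effect could take it that way.

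The sample size cannot be checked either. SD, alpha and beta do not determine n for a non-inferiority comparison of means; the distance between the margin and the true difference does the rest.

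The trial's one confirmatory conclusion is at stake. For results close to canagliflozin, the choice among plausible margins settles the verdict. According to Trial status, recruitment was expected to finish in December 2022, and the article appeared in June 2023. A margin first named after that would need a dated source to show that it preceded the data.

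**Working it through.** **Inputs from the article.** SD 0.73 in both arms, alpha 0.025, beta 0.2, 54 per arm, 10% loss and 120 in total (Sample size); 1:1 allocation (Recruitment, screening, and randomization); success required in both sets (Statistical analysis).

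**Assumptions.** Alpha is one-sided, since the article does not say. The margin M and the true difference d (LCD minus canagliflozin, positive when LCD is worse) are unknown and are varied.

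**1. The stated figures.** The inflation reproduces: 108/0.9 = 120. The 54 does not follow from the stated inputs, because the formula needs M − d:

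n per arm = 2 × SD² × (z₀.₉₇₅ + z₀.₈₀)² / (M − d)²

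with 2 × 0.73² × (1.960 + 0.842)² ≈ 8.365.

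| M (d = 0) | 8.365/M² | n, normal | n, t-based | Power at 54 per arm (t) |
|---|---|---|---|---|
| 0.30 | 92.9 | 93 | 94 | 56% |
| 0.35 | 68.3 | 69 | 70 | 69% |
| 0.40 | 52.3 | 53 | 54 | 81% |
| 0.45 | 41.3 | 42 | 43 | 89% |
| 0.50 | 33.5 | 34 | 35 | 94% |

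**2. Back-solving from 54.** M − d = 0.73 × √(2/54) × 2.802 = 0.394 (normal), or 0.397 with the noncentral t. The calculation fixes only M − d, so the solution is not unique. M = 0.30 with LCD better by 0.10 and M = 0.50 with LCD worse by 0.10 both give 54 (t-based), as does M = 0.40 with no difference. If 0.025 were two-sided, the implied M at d = 0 would be about 0.43.

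**3. Effect on the verdict.** The expected half-width of the two-sided 95% interval at 54 per arm is 1.98 × 0.73 × √(2/54) = 1.98 × 0.1405 ≈ 0.28.

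- Observed LCD deficit 0.05: upper limit 0.05 + 0.28 = 0.33. This fails at 0.30 and passes at 0.40.
- Observed LCD deficit 0.15: upper limit 0.15 + 0.28 = 0.43. This fails at 0.40 and passes at 0.50.

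**4. Secondary check: the both-sets rule.** This was a simulation of 200,000 trials per setting, with assumed M = 0.40, d = 0, a PPS nested at random in the FAS, equal exclusions in both arms, and the FAS given the information of 60 per arm (imputed values treated as fully informative).

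| PPS per arm | Exclusions from 60 | Power, PPS alone | Power, both sets |
|---|---|---|---|
| 54 | 10% | 81% | 79% |
| 51 | 15% | 78% | 76% |
| 48 | 20% | 76% | 74% |
| 45 | 25% | 73% | 71% |

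Requiring the FAS as well costs about 2 points in each row. The rest of the fall comes from the smaller PPS.

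**The case against.** The strongest reply is that an article condenses its protocol. PASS cannot return 54 without a margin and a difference, so some values were entered. Protocol V1.0 is dated July 2019, before recruitment began in December 2019, and that document and the supplementary material are not shown. The 54 also coincides with a round margin of 0.40 at zero difference.

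Much of this stands, and it rules out three inferences that a reader might draw:

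- **That no margin was ever fixed, or that one will be chosen after the data are seen.** The documents show only that none is reported.
- **That 54 is wrong.** It is unverifiable, and it is consistent with a sensible calculation.
- **That the 80% power is materially overstated because of the both-sets rule.** The 54 is what remains after 10% loss, so it may already be the per-protocol number, and joint power is then about 79%. The remark that "LCD is more life-altering and patient compliance may not be good" is a caution about one arm. It gives no exclusion rate and does not establish that the PPS will fall below 54.

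The reply does not remove the core. The margin is the decision threshold, not a detail that an article ordinarily leaves out. The Sample size paragraph reports the SD, error rates, software version and dropout, but not the quantity that drives n. The Statistical analysis section does not fill the gap with a confidence-limit rule.

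**Conclusion.** The point holds and needs correction. Followed as written, the plan cannot deliver a valid non-inferiority verdict, because it has no bound and its only stated between-group criterion is a test of difference. Across margins of 0.30 to 0.50 the required size runs from 94 to 35 per arm, and an observed deficit as small as 0.05 can pass or fail. These figures rest on SD 0.73, one-sided 0.025 and, for the sample sizes, zero true difference.

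The value 0.40 should not be read as the trial's margin. It is back-solved, other pairs of margin and difference give the same n, and adopting it because it reproduces 54 would be circular.

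The power point is secondary and conditional: about 79% if 54 is the per-protocol number, and 74% to 71% only if per-protocol exclusions reach 20% to 25%, at an assumed margin of 0.40.

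**What to change.** In Sample size and Statistical analysis:

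1. State the margin and the assumed true difference that were actually entered in the PASS calculation, citing protocol V1.0 or the calculation record, with the date and a clinical justification. Use 0.40 only as a value to check against. If no dated margin exists, say so.
2. State that alpha 0.025 is one-sided. If the calculation was run otherwise, report that.
3. For the primary outcome, replace the P < 0.05 test of difference with this rule: non-inferior if the upper limit of the two-sided 95% confidence interval for LCD minus canagliflozin in HbA1c change lies below the margin, in both FAS and PPS.
4. Say which analysis set the 54 per arm refers to. If per-protocol exclusions above 10% are expected, restate the power for the both-sets rule at the expected PPS size.

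The cost is wording, best done before database lock, and possibly a slightly lower stated power. No extra patients are needed.

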### Recruitment, screening, and randomization

T2DM patients with poor blood glucose control will be recruited at three hospitals in Shanghai and Ningbo, China. First, clinical endocrinologists will introduce the purpose, risks, and benefits of the study to T2DM patients. Then, researchers will communicate with those interested in the trial and confirm whether they meet the inclusion and exclusion criteria. Finally, informed consent will be obtained, and the initial visit will start.

The table of random numbers will be generated by a statistician with particular random seeds. Variable block sizes of 4 and 6 will be used and stratified by whether HbA1c is between 7.5% and 8.5% or above 8.5% and whether the patients have taken antihyperglycemic agents in the past 3 months. Sealed envelopes containing group information will be prepared. The sequence number for each stratification will be typed on the surface of the envelope. The researchers will open the envelopes according to the sequence of enrollment and identify the group. Participants will be randomly assigned in a 1:1 ratio to the canagliflozin or LCD group. Each participant will have a unique study number.

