### Data collection and confidentiality

Researchers at each center will collect data according to the timeline schedule shown in Table 2. Researchers from each center will receive their own account to upload data and will be blinded to other centers.

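### Envelopes are numbered by HbA1c and drug stratum without centre, so balance across three competitively enrolling hospitals is not assured and the sharing of each sequence is not described

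*Protocol article*

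**What the plan says.** All of the following is from the protocol article.

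- **Recruitment, screening, and randomization** gives the block sizes ("Variable block sizes of 4 and 6 will be used") and the strata: "stratified by whether HbA1c is between 7.5% and 8.5% or above 8.5% and whether the patients have taken antihyperglycemic agents in the past 3 months". Two factors with two levels each make four strata. Centre is not among them.
- The same section describes the envelopes ("The sequence number for each stratification will be typed on the surface of the envelope") and their use: "The researchers will open the envelopes according to the sequence of enrollment and identify the group". Researchers also confirm eligibility.
- It places recruitment at three sites: "T2DM patients with poor blood glucose control will be recruited at three hospitals in Shanghai and Ningbo, China". **Design** adds: "Competitive enrollment was used to recruit participants, with an allocation ratio of 1:1 for the canagliflozin and LCD groups".
- **Data collection and confidentiality** says: "Researchers from each center will receive their own account to upload data and will be blinded to other centers".
- **Data management and quality control** gives the Clinical Research Center a part in coordinating the centres, but states no role in allocation. All data go into one web database.
- **Statistical analysis** compares groups at endpoint by an independent t-test or Mann–Whitney test, with no term for centre.

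**The concern.** The article spells out the allocation procedure, and two parts do not meet. A number that runs within a stratum and is used in order of enrolment implies one queue per stratum for the whole trial. Paper envelopes opened by researchers at three hospitals imply several queues. If the four sequences are shared, a site needs to learn which number is next, and no mechanism is given. If complete sets are issued per hospital, centre becomes a stratifying factor in fact, although the article does not list it. If four lists are divided among hospitals, blocks may be split.

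Centre could matter for HbA1c. The diet arm depends on one-on-one consultations and individual instructions, and an endocrinologist directs reductions in background drugs. Both may differ between hospitals. Neither the stated strata nor the stated test takes account of that. In addition, the arms are visibly different (a diet or a drug), and researchers both judge eligibility and open the envelopes. How well the next assignment can be guessed therefore also matters.

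**Working it through.** **Inputs from the article.** Three hospitals; 1:1 allocation; blocks of 4 and 6; four strata; SD of HbA1c change 0.73; 54 per group before loss. The total reproduces: 54 / 0.9 = 60 per group, 120 in all. The article gives no figure for balance by centre, so there is none to reproduce there.

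**Assumptions, not in the article.** Four equally likely strata, block sizes 4 and 6 equally likely, patients arriving from the centres in random order, and centre sizes of 40/40/40, 60/30/30 or 80/20/20.

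**1. Balance by centre with one shared list per stratum.** Allocation was simulated and runs counted in which at least one centre had |n1 − n2| / n ≥ 0.30, that is 65:35 or worse.

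| Centre sizes | Chance that some centre is at 65:35 or worse |
|---|---|
| 40/40/40 | about 9% |
| 60/30/30 | about 11% |
| 80/20/20 | about 39% |

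Repeat runs moved these by one or two points. The last row comes from the small centres, where 65:35 means 13 against 7 of 20.

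In absolute numbers, with assumed site shares of 33/33/33, 50/30/20 and 70/20/10, the arms within a centre differ on average by 2.6 to 4.5 patients. A gap of 10 or more at some centre occurs in 9–16% of runs. With one list per stratum and centre (4 × 3 = 12 lists), the mean gap is about 1.6 and a gap of 10 or more is practically absent. The overall arm difference rises from about 1.5 to about 2.7–2.8.

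**2. Effect on the primary estimate.** Standard error of the difference with 60 per arm: 0.73 × √(2/60) = 0.133. Take one 20-patient centre split 13 to 7. Its share of the arms differs by 13/60 − 7/60 = 0.10. If its patients differ from the others by an assumed 0.3 HbA1c points, the estimate shifts by 0.10 × 0.3 = 0.03, about a quarter of the standard error (0.03 / 0.133 = 0.23).

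**3. Gain from a centre term.** With centres assumed 0.3 HbA1c points apart and within-centre SD 0.73, the simulated standard error is about 0.14 unadjusted and about 0.13 with a centre term when centres are of equal size. The gain is smaller when one centre dominates. Three centres cost 3 − 1 = 2 degrees of freedom.

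**4. Guessing the next arm.** The strategy is to guess the arm that has so far been used less in that stratum.

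| What the site researcher sees | Correct guesses |
|---|---|
| Shared list, own site's allocations only | about 54–56% |
| Separate list per centre, blocks of 4 and 6 | about 67% |

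An observer who sees every earlier allocation in a stratum and knows the block sizes reaches about 69%.

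**The case against.** The strongest reply is that a condensed article commonly leaves to the full protocol who holds the envelopes and how they are divided. Each hospital could hold its own numbered set, or one holder could release the next envelope by telephone, and the article excludes neither. Leaving centre out of the strata is a legitimate choice when 120 patients already fall into four strata, and adjustment for centre may stand in an analysis plan that is not shown. Chance imbalance does not bias a randomised comparison.

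Much of this stands, and it rules out four stronger readings:

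- A reader might infer that the procedure cannot be carried out. The text does not show that; it only omits the mechanism.
- A reader might take the statement that researchers are blinded to other centres as proof that a site cannot know the next number. That sentence concerns accounts for uploading data, not enrolment order or envelopes.
- A reader might conclude that the arms are unbalanced by site. Balance is only not assured, and if complete per-site sets were used it would hold within block limits.
- A reader might apply the 69% guessing rate. It needs sight of all hospitals' allocations, which a site drawing on a shared list would not ordinarily have.

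What the reply does not remove is that the article lists the strata without centre and names an unadjusted test. Those are stated choices, and the second can be improved at almost no cost.

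**Conclusion.** The point holds in a limited form. The article fixes four strata without centre and paper envelopes numbered by stratum. With three competitively enrolling hospitals, a shared sequence needs coordination that is not described, and balance by centre is not assured. The chance of a 65:35 split or worse at some centre is roughly 10–40%, depending on centre sizes that the article does not give. Randomisation remains valid. The expected shift in the HbA1c difference is small: about 0.03 against a standard error of 0.13, under an assumed centre effect of 0.3. The case for change rests on its low cost, not on a demonstrated bias.

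**What to change.** For all participants:

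- Include centre as a term in the primary HbA1c comparison in place of the unadjusted test.
- Report the number in each arm by centre.
- State how the envelopes were held or divided among the hospitals.

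This is the part most likely to be usable, because the Trial status section expected recruitment to be complete in December 2022, before the article appeared in June 2023.

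For anyone still to be randomised, keep the four shared lists but release the next assignment centrally, through the existing database or the Clinical Research Center, only after eligibility and stratum have been entered. This keeps each sequence in order and the next assignment concealed from the sites.

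Per-centre lists or envelope sets with blocks of 4 and 6 should not be adopted without stating their price. They nearly remove imbalance by centre, but raise a site's chance of guessing the next arm from about 55% to about 67% and leave more incomplete blocks across 12 lists.

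The cost is one log-in or call per assignment, 2 degrees of freedom in the analysis, and a short amendment.
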